## Energy expenditure

RMR*.* Indirect calorimetry will be performed before the assessment of insulin sensitivity/secretion using a Deltatrac II Metabolic cart (Datex-Ohmeda, Helsinki, Finland) over a 45-min. period. The analyzer will be calibrated before each study with standardized gases containing 5% CO2 and 95% O2. After quietly resting for 5-10 minutes, a transparent plastic hood connected to the device will be placed over the head of the subject. Calculations of O2 consumption and CO2 production will be made from continuous measurements of CO2and O2 exchange over 45 minutes. Subjects will be asked to remain motionless and awake during the test and the last 30-min. of the measurement will be used to calculate RMR. The rate of protein oxidation will be determined from the rate of urinary urea production and the rates of carbohydrate and lipid oxidation according to Elia and Livesey154,155**.**

Metabolic Chamber. 24-h energy expenditure and substrate oxidation will be measured in a metabolic chamber at baseline and at each block of testing. Volunteers will enter the chamber at 7:45 AM after an overnight fast, and leave the chamber at 7:00 AM the next morning. During their stay in the chamber, no exercise will be allowed. Meals will be served according to a fixed schedule. Microwave motion detectors provide continuous monitoring of the volunteers’ spontaneous physical activity. The 2 metabolic chambers, each of which measure 10’x14’x8’, corresponding to a volume of 27,000 L, were designed to provide a pleasant ambiance for study volunteers. The rooms have two windows, and are furnished with a bed, desk and chair, television, radio/tape player, telephone, microwave, sink and toilet with privacy curtain. Once a mo., the accuracy and precision of the calorimeters are assessed by 24-h propane combustion tests.

The Pennington Metabolic Kitchen staff will prepare all food consumed in the chamber. At baseline, the energy content will be estimated according to a previously developed equation and adjusted during the day on the basis of the energy expenditure of the first 7 hrs. of measurement 156. After the baseline recording, energy content of the food for the subsequent chamber measures will be calculated as 100%, 87.5%, or 75% of baseline 24-h measured energy expenditure, according to the study arm. 24-h urine will be collected for norepinephrine and cortisol excretion rates determinations. During each stay in the chamber, subjects will be asked to fill visual analogue scale (VAS) to measure hunger, satiety, fullness and desire to eat during the course of the day. These VAS tools, first developed by Blundell have been fully validated 157 and used in association with plasma leptin changes in relation to daily changes in hunger and satiety 158. Core temp. will be measured and recorded every 5-min. during the 24 hrs. of energy expenditure measurements in the chamber. At 7:00 AM the volunteers will swallow a 10 x 20-mm silicone coated radio-capsule (Human Technologies, Inc St Petersburg, FL) and will be fitted with a bandoleer type antenna system, connected to a portable monitor that records core temp.

Doubly-labeled Water*.* On Day 0, a fasting baseline urine sample is collected, a metabolic weight taken and a DEXA scan performed. Following this, subjects will drink from a stock solution with 0.22g/kg total body water (TBW) of H218O (Cambridge Isotopes, Cambridge, MA) and 0.115 g/kg TBW of 2H2O (Isotec Inc., Miamisburg, OH or Cambridge Isotopes, Cambridge, MA), followed by a 100-200ml of tap water used to rinse the dose container. Following 2 voids, two consecutive urine samples are collected (at 4 and 6.5 hours after dosing). For the next 14 days after dosing urine samples are collected each morning after breakfast. On Day14, a metabolic weight and DEXA scan is repeated. Additional DLW measurements may be used to monitor compliance periodically throughout the study (at 1 month for Phase 1). Urine samples will be collected on days 0, 7 and 14 only for these additional measurements.

The 2H and 18O isotope elimination rates (kH and kO) will be calculated using linear regression using the isotopic enrichment relative to predose enrichment of the urine samples from the beginning (days 1 and 2 postdose) and end of the metabolic study (days 13 and 14). Total body water will be determined form the enrichment at time zero, obtained from the regression line. The rate of CO2 production is calculated using the equations of Schoeller et al. 159 and later modified 160 as follows: rCO2 = (N/2.078)(1.007kO‑1.041kH)‑0.0246rH2Of,, where N is the total body water and rH2Of is the rate of fractionated evaporative water loss which is estimated to be 1.05N (1.007kO ‑ 1.041kH). Energy expenditure is calculated by multiplying rCO2 by the energy equivalent of CO2 for an assumed RQ of 0.882 (food quotient of the diet) and estimated changes in body energy stores as previously described 161. We will also take into account the 24-h RQ measured a few days after in the respiratory chamber. Energy intake will also be estimated by subtracting energy expenditure from the change in body weight (kg) and body composition (DEXA) over the 14 day period according the methods of Schulz 162.

Exercise efficiency.Whole-body exercise efficiency will be determined using measures of O2 consumption and CO2 production (Vmax, Sensormedics, Yorba Linda, CA) obtained in the steady-state during the 3rd and 4th min of three workloads on a bicycle ergometer, i.e. 40, 80 and 120 watts at 60 rpm (or 30, 60 and 90 watts if necessary). Respiratory exchange will also be measured at baseline in resting conditions sitting on the bike and at freeload pedaling at 60 rpm. Delta efficiency will be calculated using the slope of the regression line between oxygen consumption and external workload 163.

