## Overall Description of the Experiment

The proposed study is a 6 mo. study to be completed over a period of 2 yrs. The study will involve 60 overweight healthy male and female volunteers divided into four equal groups matched for age and gender. As shown in figure 1, the four groups include:

Group 1: Controls (No CR but receiving a healthy diet as per the American Heart Association recommendations)

Group 2: CR (energy deficit 25%)

Group 3: CR 12.5% + PA 12.5% (energy deficit 25%)

Group 4: CR (LCD 800 kcal balanced liquid diet) followed after a 15% wt. reduction by wt. maintenance (“wt. clamping”).

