After baseline testing and randomization, the target calorie level for each participant is determined. This is achieved by measuring energy expenditure by doubly labeled water (twice at baseline, once whilst the participant is consuming usual diet at home, and once whilst consuming meals provided by PBRC metabolic kitchens) and by the metabolic chamber, baseline feeding requirements and the assigned study intervention. The LCD participants will be fed 800kcal/day regardless of energy requirements until 15% weight loss is achieved. Following this the “weight clamped” subjects will be fed or prescribed a similar diet providing the necessary energy to maintain the 15% wt. loss. Subjects receiving less than 1800 kcals/day will be provided with a multi-vitamin supplement to ensure adequate nutrition is maintained during energy restriction. This will be monitored by pill counts each month.

*Menu Development*. Menus are developed by the metabolic kitchen research dietitians, and are analyzed using the MENu (Moore's Extended Nutrient) database. Recipes are selected to include regional food preferences to increase dietary adherence. The research dietitian reviews the finalized menu with each potential participant before the research project begins. The participant's food likes, dislikes and intolerances, including food allergies, are discussed. If necessary, foods that a participant refuses to eat are substituted with an equivalent food item. Individual choices, within study limitations, are given for beverages throughout the study.

*Diet Distribution*. Daily food production sheets for each participant are used, listing day, menu cycle, meal, food items required with portion weights, and special dietary requirements. When preparing the meal trays, the food production sheets are followed. Additionally, foods are labeled for participant identification. Foods are placed on individual meal trays until served, or are individually packaged for take-out, following tray assembly forms. At the time of meal pick-up, the hostess reviews the menu with the participant, checking off the foods to confirm all are provided. Meals are served to the participant on test days only after all study procedures have been completed. A meal ticket is given to the participant by an authorized nurse or scientist, which is presented to the hostess.

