Individual tailoring of treatment. One aspect of lifestyle behavior modification, i.e. frequent and regular therapeutic contact, has been found to be very important for long-term behavior change. To accomplish frequent contact, treatment will be tailored to the needs of the individual participant using internet-based contact and/or telephone contact. Also, for persons who are having difficulty following the prescribed dietary or PA program, the intervention will be tailored to address the unique problems of the individual. The rate of predicted weight loss will be calculated using a 2-reservoir dynamic model of the energy balance equation as described by Alpert 128. This data will be used to monitor compliance and will not be shared with the volunteer. Metabolic weight will be measured once per week. Participants who fail to meet 60% of the expected rate of wt. loss will be interviewed very carefully to identify reasons for potential sup-optimal compliance with the prescribed treatment. Compliance will also be assessed by measures of metabolic rate, heart rate monitors, accelerometers and doubly labeled water. If problems related to compliance are identified, solutions to the problem will be established and individualized interventions will be initiated and tested for specified periods of time. If these interventions result in hypothesized changes in weight, they will be continued; if not, new strategies will be formulated and tested until success is achieved. Only after different tries, subjects will be asked to leave the study.

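### The protocol states the labeled-water energy intake estimate with the wrong operation: as written it is negative for every participant and mixes kilograms with kilocalories

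*Protocol*

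**What the plan says.** The relevant text is the Doubly-labeled Water paragraph under Energy expenditure in the Protocol.

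- **Expenditure.** "Energy expenditure is calculated by multiplying rCO2 by the energy equivalent of CO2 for an assumed RQ of 0.882". This is a positive quantity. The same sentence also mentions estimated changes in body energy stores and cites a source for them.
- **Intake.** The sentence opens "Energy intake will also be estimated by subtracting energy expenditure from the change in body weight (kg" and, after closing the unit bracket, continues "and body composition (DEXA) over the 14 day period according the methods of Schulz 162". It names no energy equivalents for fat or fat-free tissue and no sign convention for the change.
- **Use of labeled water.** Under Timeline (individual tailoring): "Compliance will also be assessed by measures of metabolic rate, heart rate monitors, accelerometers and doubly labeled water". Under Energy expenditure: "Additional DLW measurements may be used to monitor compliance periodically throughout the study". Both name the method. Neither says that the intake derived from it is the compliance measure.
- **Prescribed deficits.** Overall Description of the Experiment sets a 25% deficit for the CR arm ("Group 2: CR (energy deficit 25" percent) and for the combined arm ("Group 3: CR 12.5% + PA 12.5% (energy deficit 25" percent). For the low-calorie arm, Diets and diet delivery says: "The LCD participants will be fed 800kcal/day regardless of energy requirements until 15% weight loss is achieved".

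**The concern.** Intake, expenditure and stores are tied by one identity: what is eaten equals what is spent plus what is stored. The sentence subtracts expenditure where it should be added, and one of its terms is in kilograms. Someone who programs the sentence as it stands cannot obtain a valid intake for anyone.

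The estimate has a real use here. Overall Description of the Experiment says the study tests feasibility of, and compliance with, a 25% restriction, and Hypothesis E lists compliance among its measures. Meals come from the Center for about the first 3.5 months. In months 4 to 6 the diet is self-selected and recorded in food diaries. Labeled water is dosed again at 6 months, so the labeled-water and DEXA balance is the only intake estimate described for that phase that does not rest on self-report.

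**Working it through.** The protocol gives no numerical intake figure to reproduce, so the check is algebraic, with an illustration.

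**Inputs**
- Deficits of 25% (CR) and 12.5% + 12.5% (CR+PA): Overall Description of the Experiment.
- 800 kcal/d for the low-calorie arm: Diets and diet delivery.
- Weight-clamped intake 20–25% below baseline requirement: Overall Description of the Experiment (20% used here).
- Baseline expenditure: **assumed** 2,500 kcal/d, with a range of 1,800 to 3,400 taken from the lowest and highest prepared diet levels.
- A 10% fall in expenditure in one row: **assumed**, equal to the 10% decrease considered in the power section.

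**Formulas** (EE = expenditure, EI = intake, ΔS = daily change in body energy stores, end minus start, so losses are negative)
- Energy balance: EI = EE + ΔS
- Rule as written, granting that the change has been converted to kcal/d: ΔS − EE
- Error of the written rule: (ΔS − EE) − (EE + ΔS) = −2 × EE

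**Results at baseline EE of 2,500 kcal/d, full adherence**

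| Situation | EE | True EI | ΔS = EI − EE | As written, ΔS − EE | Balance, EE + ΔS | Error |
|---|---|---|---|---|---|---|
| Control, weight-stable | 2,500 | 2,500 | 0 | −2,500 | 2,500 | −5,000 |
| 25% CR, EE unchanged | 2,500 | 1,875 | −625 | −3,125 | 1,875 | −5,000 |
| 25% CR, EE down 10% | 2,250 | 1,875 | −375 | −2,625 | 1,875 | −4,500 |
| CR+PA | 2,812.5 | 2,187.5 | −625 | −3,437.5 | 2,187.5 | −5,625 |
| Low-calorie diet | 2,500 | 800 | −1,700 | −4,200 | 800 | −5,000 |
| Weight-clamped, 20% below | 2,000 | 2,000 | 0 | −2,000 | 2,000 | −4,000 |

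Over baseline EE of 1,800 to 3,400 the written rule stays negative in every row. The least negative value is −1,440 (clamped: 0 − 0.8 × 1,800) and the most negative is −6,000 (low-calorie diet: (800 − 3,400) − 3,400).

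**Sign convention.** If the change is entered as start minus end, so that a loss is positive, the CR row becomes 625 − 2,500 = −1,875, the true intake with its sign reversed. The result is negative under either convention.

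**Units.** Without conversion, a 1 kg loss over 14 days (illustrative) would be entered as −1 against 2,500 × 14 = 35,000 kcal. The body-store term would then contribute almost nothing.

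**The case against.** **The sentence defers to a cited method.** That source is not available here, so the planned calculation may be correct and only the one-line paraphrase wrong. This stands, and it limits the point to the wording. It does not clear the wording, because the operation described still conflicts with energy balance. The energy equivalents themselves can reasonably be left to the cited method or to an analysis plan.

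**A negative intake would be noticed at the first calculation.** This also stands. The literal rule could not silently pass as a plausible value.

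**A reader might infer that compliant restricted participants would be classed as overeating, with no error in controls.** That needs a different formula, EE − ΔS, reached by dropping the minus sign. For the CR row it gives 2,500 + 625 = 3,125 against a true 1,875. The excess of 1,250 is twice the deficit, and it is zero at stable weight. The protocol does not state that formula. Dropping the sign under the opposite convention returns the correct 1,875. For the written rule, with change taken as end minus start, the error is −2 × EE in every arm, controls included. It follows expenditure, not weight loss.

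**No decision rule uses this intake.** The numerical compliance triggers rest on body weight: 60% of the expected rate of loss (Timeline) and 15% loss by 14 weeks in the low-calorie arm (Diets and diet delivery). The diet compliance score comes from food diaries. Calorie targets use measured expenditure, baseline feeding requirements and the assigned intervention. This stands in full.

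**Conclusion.** The intake rule is wrongly stated, and that can be seen from the text alone. With change taken as end minus start, the written value is too low by twice the participant's expenditure: 5,000 kcal/d at an assumed 2,500, and 3,600 to 6,800 kcal/d for expenditures of 1,800 to 3,400. It is negative for everyone under either sign convention, and its units do not match. The kcal figures rest on assumed expenditures; the sign and the algebra do not.

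The consequence is limited to a supporting estimate that bears on adherence to the 25% deficit. The primary endpoint is expenditure, which is obtained without this sentence. Table 2 and the power calculation do not use intake, and labeled-water intake is not one of the seven listed secondary outcomes. Misclassified compliance, or a bias confined to the restricted arms, might be inferred, but neither is shown: no cut-off uses the estimate, and the arm-specific inflation belongs to a formula that the protocol does not give. This is a minor correction, certain as to the wording; the documents do not show how the calculation would be done in practice.

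**What to change.** Replace the intake sentence in the Doubly-labeled Water paragraph with one to this effect:

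*Energy intake (kcal/d) = labeled-water energy expenditure (kcal/d) + (change in fat-mass energy + change in fat-free-mass energy, kcal)/14, the changes taken from DEXA on days 0 and 14 as end minus start, so that losses are negative, and converted with the energy equivalents of the cited method.*

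Before adopting it, the investigators should confirm that the cited method performs this operation and that any existing program does so too. The cost is one sentence and that check. Both DEXA scans are already scheduled in the paragraph, so no new data, visits or changes to other analyses are needed.

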**Oxidative Stress**

***DNA Damage***

Comet Assay for DNA damage – Single-cell gel electrophoresis (SCGE, comet assay) provides a very sensitive method for detecting strand breaks and measuring repair kinetics at the level of single cells 56. A variety of possible modifications to the assay facilitate the detection of single-strand breaks, incomplete excision repair sites, and interstrand cross-links. In addition to the above, DNA fragmentation associated with cell death or related to apoptosis can be evaluated with the comet assay. After initial treatment, cells are embedded in agarose layers, lysed, and electrophoresed. After staining with a fluorescent DNA binding dye, cells with increased DNA damage display increased DNA migration from the nucleus toward the anode, thus forming the shape of a “comet”. The comet assay takes 2 days and utilizes a small number of cells. Briefly, lymphocytes are suspended in low melting point agarose and immobilized on slides. The slides are then treated with a gentle lysing solution, followed by a highly alkaline solution (>pH 12.6) to expose AP and other alkali labile sites. Alternatively, lysed cells can be treated with DNA glycosylases to reveal damaged DNA bases. The slides are then placed into an electrophoresis chamber. Following electrophoresis, the slides are fixed and stained. For quantification, digital imaging will be used. There is a commercially available kit from Trevigen for conducting the comet assay and the DNA repair proteins we propose to use are routinely purified in [name] laboratory.

Determination of baseless sites in DNA – The action of ROS destabilize DNA bases that result in the formation of baseless DNA (apurinic/apyrimidinic=AP). These baseless sites also arise as an intermediate in the repair of ROS damaged DNA bases such as 8-oxoguanine. A specific method for the detection of AP sites has been developed and is currently in use in [name]’s laboratory. This method utilizes the reagent O-(carboxymethyl) hydroxylamine that has been reacted with biotin hydrazide in the presence of carbodimide. Aldehyde reactive probe (ARP) specifically reacts with AP sites in DNA, identifying them with biotin residues. The biotin-marked AP sites are determined using a color detection system in a slot-blot or ELISA type analysis and avidin/biotin complex conjugated to horseradish peroxidase. This system has been modified to use the more sensitive chemiluminescence detection kits (Boehringer-Mannheim) in a slot-blot apparatus. One AP site for every 10,000 bases of DNA (approximately 10fmol of AP sites) can be detected and requires as little as 300ng of DNA per reaction. Band densities are normalized with GAPDH expression.

Determination of 8-oxoguanine for DNA Damage - DNA isolated from lymphocytes will be used to determine the amount of 8-oxoG using gas chromatography-mass spectroscopy (GC-MS) with selected ion monitoring (SIM). Briefly, extracted DNA will be enzymatically hydrolyzed. Derivatization of the hydrolyzed DNA will be carried out using bis(trimethylsilyl)trifluoroacetamide (BSTFA) containing 1% trimethylchlorosilane and acetonitrile (1:1) in a total volume of 70 ml at 130°C for 20 min in vials flushed with nitrogen. Derivatized samples will then be injected into the GC-MS using SIM. Quantification of the modified DNA base will be carried out using specific ions eluting from the GC column. The stable isotope for 8-oxoG is already in use. Alternatively, urine samples could be evaluated for the presence of the free 8-oxoG base using GC-MS.

Isoprostanes. The isoprostane that has been most often studied (shown to be a potential marker for oxidative stress) is 8-epi PGF2 alpha, although there are several names for this compound. We will measure 8-epi PGF2 alpha as an isoprostane marker of oxidative stress 164 using HPLC/MS-MS. Briefly, an internal standard (deuterated 8-epi PGF2 alpha, Caymen Chemical) will be added to urine, followed by addition of 15% KOH and allowed to stand for 30 min. The sample is then subjected to solid phase extraction after adjusting pH. The sample is dried and resuspended in 20% acetonitrile in water and subjected to HPLC MS/MS. We have analyzed several isoprostanes, including 8-epi PGF2 alpha using our HPLC MS/MS (Finnigan TSQ 7000) and are currently piloting the method in smokers vs. non-smokers.

Carbonyl Content. Serum samples will be analyzed for carbonyl content, an indicator of oxidative damage to proteins. The method was described by Reznick and Packer 165. Briefly, serum samples are combined with 2,4 dinitrylphenylhydrazine. The carbonyls in the sample react with the 2,4 DNP to form protein hydrazones. The product is measured spectrophotometrically at 355-390. Each sample is scanned against a sample treated with 2.5 M HCl. Carbonyl content is calculated from the absorption spectra using an absorption coefficient of 22,000 M-1 cm –1.

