An abundant form of DNA damage by free radical attack is 8-oxyguanine [8-oxoG]50. Its formation can lead to GT transversion mutations 51 since Adenine is misincorporated opposite 8-oxoG during DNA replication 52. Free radical attack on DNA can also give rise to baseless, or apurinic/apyrimidinic (AP), sites. The most likely mechanism for this observation is that the DNA damage produced by oxidative stress results in destabilization of the N-glycosylic bond and the formation of an AP site. Moreover, the repair of 8-oxoG can give rise to AP sites as an intermediate in their repair. The presence of AP sites in DNA can be lethal to the cell 53, or cause mutations 53,54. Notably, the formation of both 8-oxoG and AP sites increase with age 55,56. Therefore, DNA damage from oxidative stress produced by energy metabolism is a potential cause of natural aging.

In the present study, we propose to measure protein carbonylation, isoprostanes as an index of lipid peroxidation, and DNA damage by the comet assay and the urinary excretion of 8-oxoguanine. We will test the hypothesis that CR will decrease damages to protein, lipid and DNA.

##

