- **Hypothesis D**. Chronic CR is associated with adaptations in the expression of genes involved in aging, including those related to oxidative stress, energy metabolism (carbohydrate, lipid and protein), and longevity.

**Aims**: Measure for differences in the expression of candidate genes in skeletal muscle and adipose tissue.

- **Hypothesis E**. Psychophysiologic outcomes are improved when the energy deficit is produced by combining PA and CR compared to CR alone.

**Aims** : Measure for differences in weight loss, compliance, rate of drop out, quality of life (QOL), mood, cognitive function, fitness & strength, reaction times, physical activity & food records, and risk of developing an eating disorder.

| **CHARACTERISTICS OF THE SUBJECT POPULATION** |
| --- |

Sixty subjects will be recruited for this study. Only subjects with a 25 ≤ BMI < 30 and 25 ≤ age < 50y for males and 25-45 for females will be included. The lower age limit for females is to avoid the confounding effect of menopause. We will make a conscious effort to enroll 50% males and 50% females. The ethnic/racial composition of the subjects will be proportional to that of Baton Rouge. We expect, therefore, to enroll approximately 20-25% African Americans in the presented study. Female subjects will be checked for pregnancy on a regular basis (each block of testing) and will be discharged from the study if pregnant. The following inclusion/exclusion criteria will also be followed:

Inclusion

- Healthy men and women
- 25 ≤ BMI < 30
- 25 ≤ age < 50 for males
- 25 ≤ age < 45 for females (women age 40-45 will be screened for menopause)

Exclusion

- Personal history of CVD or elevated blood pressure (>160/90 mmHg)
- Personal history of diabetes
- Personal history of major psychiatric disorders
- Personal history of eating disorder
- Post obese (never have had a BMI > 32)
- Smoking
- Subjects exercising regularly (> twice per week)
- Regular use of medications except oral contraceptives
- Individuals with alcoholism or other substance abuse
- Pregnancy or lactation
- Abnormal EKG
- Individuals who have been resident in the greater BTR for < 1y
- Individuals in occupations requiring full alertness and motor skills (airline pilots, etc.) where even a small chance of postural dizziness would be unacceptable

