## Outcome measures

**Primary outcome**. The primary endpoint will be the rate of energy expenditure under resting, sedentary and free living conditions. Each component will be assessed by state-of-the-art methods (ventilated hood, respiratory chamber and doubly labeled water). Sedentary energy expenditure in the respiratory chamber has been used for the power analysis. The reason is that this method is the most sensitive for assessing all of the components of daily energy expenditure, except for the cost of voluntary activity under free living conditions, and is therefore the most likely to uncover differences in energy expenditure for weight maintenance induced by chronic CR. As shown in Table 2, 5-11 subjects are sufficient to detect a 10% decrease in absolute or adjusted 24-h energy expenditure. Furthermore, assuming an intra-subject variability of 7.5%, a 15% decrease in total daily energy expenditure can be detected by doubly labeled water with only 11 subjects per group. With 15 subjects enrolled per arm in the study, we feel confident that we will have the necessary power of detecting significant decreases in both sedentary and total daily energy expenditure.

**Secondary outcomes**. While the proposed studies have sufficient power to detect differences for the primary endpoint, because of the novelty and opportunity offered by this study, we also plan to monitor several secondary outcomes of interest in a more descriptive manner. However, the methods and number of subjects may not always be up to the task of uncovering suspected differences.

1. Changes in body composition. We hypothesize that approximately 2/3 of wt. loss during CR will be fat mass, but more (75%) when a combination of CR and increased PA is the cause of similar negative energy balance. Body composition will be measured by DEXA, the new gold standard. Because of the precision and reliability of the method, small differences in changes in fat mass and fat-free mass can be detected.
2. Changes in oxidative stress. At baseline and at different phases of the study, oxidative stress will be measured indirectly by DNA damage, lipid peroxidation (isoprostanes), and protein carbonylation.

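### The AP-site assay for DNA damage is normalised to GAPDH expression, which does not measure how much DNA was loaded

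*Protocol*

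**What the plan says.** The relevant text is in the protocol's Oxidative Stress section, under DNA Damage, in the paragraph on baseless sites.

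- **What is detected:** "Aldehyde reactive probe (ARP) specifically reacts with AP sites in DNA, identifying them with biotin residues".
- **Sensitivity:** "One AP site for every 10,000 bases of DNA (approximately 10fmol of AP sites) can be detected".
- **Input:** the method "requires as little as 300ng of DNA per reaction".
- **Normalisation:** "Band densities are normalized with GAPDH expression".

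No DNA-based normaliser and no fixed DNA load is stated for this assay.

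On the role of the measurement, the Outcome measures section lists oxidative stress among the secondary outcomes: "oxidative stress will be measured indirectly by DNA damage, lipid peroxidation (isoprostanes), and protein carbonylation". The secondary outcomes as a group are to be followed in a more descriptive way than the primary endpoint. Aim A2 under Hypothesis A covers oxidative damage to DNA, protein and lipid. The Overall Description of the Experiment gives validation of the DNA oxidative stress measure as one of the methods to be piloted for a longer study.

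**The concern.** The probe, the sensitivity and the input all refer to DNA, so the quantity of interest is AP sites per unit of DNA. The normaliser refers to something else. How strongly a gene is expressed in a sample does not say how much DNA went into a slot.

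Two things follow if a laboratory applies the sentence as written. First, variation in GAPDH expression between subjects and visits enters the reported damage value as noise, while variation in DNA load is not corrected for. Second, if the intervention alters GAPDH expression in the assayed cells, that change would appear as a change in DNA damage, or would mask a real one.

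At stake is the interpretation of one oxidative-damage measure under Aim A2. Because the study is also meant to settle methods for a longer trial, a wrong denominator could be carried forward.

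**Working it through.** The protocol gives no numerical result for this assay to reproduce. The check is to compare the stated quantities and then do ratio arithmetic.

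**Step 1. Units.**

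| Element of the assay | Refers to |
| --- | --- |
| Probe target | AP sites in DNA |
| Sensitivity | AP sites per 10,000 bases of DNA |
| Input | mass of DNA, at least 300 ng |
| Normaliser | GAPDH expression (RNA or protein) |

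The first three agree. The fourth does not belong with them.

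**Step 2. What each denominator returns.** Let *a* be AP sites per unit of DNA, *m* the DNA loaded and *E* the GAPDH expression. The band signal is proportional to *a* × *m*.

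- Divided by DNA loaded: (*a* × *m*) / *m* = *a*, the intended quantity.
- Divided by GAPDH expression: (*a* × *m*) / *E*. The load *m* does not cancel, and *E* is added as a further source of variation.

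**Step 3. Effect of a shift in GAPDH expression.** Hold the load constant. Let the intervention multiply true AP sites per unit of DNA by *d* and GAPDH expression by *g*. The reported fold change is *d*/*g*; with a DNA denominator it is *d*. The documents give no value for *g*, so the values below are assumptions, chosen only to show how the ratio behaves.

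| Assumed *g* | Reported change, AP sites unchanged (*d* = 1) | Reported change, true 10% fall (*d* = 0.9) |
| --- | --- | --- |
| 0.8 | 1/0.8 - 1 = +25.0% | 0.9/0.8 - 1 = +12.5% |
| 0.9 | 1/0.9 - 1 = +11.1% | 0.9/0.9 - 1 = 0.0% |
| 1.0 | 0.0% | -10.0% |
| 1.1 | 1/1.1 - 1 = -9.1% | 0.9/1.1 - 1 = -18.2% |
| 1.2 | 1/1.2 - 1 = -16.7% | 0.9/1.2 - 1 = -25.0% |

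With a DNA denominator every row would read 0% in the second column and -10% in the third.

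**Step 4. Does the protocol predict *g* different from 1?** Hypothesis D says "Chronic CR is associated with adaptations in the expression of genes involved in aging", and it counts energy-metabolism genes among them. Its stated aim, however, is to measure expression in skeletal muscle and adipose tissue. The paragraph on baseless sites does not name its DNA source, and the neighbouring comet and 8-oxoguanine assays use lymphocytes. No passage says how GAPDH behaves under caloric restriction in any tissue, and the list of 49 candidate genes is in an appendix that is not shown. The protocol therefore neither predicts a shift in the assayed cells nor gives a reason to rule one out.

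**The case against.** The strongest reply is that the sentence is loosely worded and not a real analysis choice. The sample on the blot is DNA, so normalising its bands to GAPDH may mean a genomic GAPDH probe used as a loading control. On that reading the denominator does measure DNA and there is no error beyond the word *expression*. The sentence may also have strayed in from an RNA or protein blot method. Either is possible. Neither is what is written, and both call for the same correction.

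A second reply concerns reach, and it stands. Energy expenditure is the primary endpoint, and oxidative stress is secondary. The background section on oxidative stress, where it says what will be measured, names "DNA damage by the comet assay and the urinary excretion of 8-oxoguanine" and does not mention the AP-site assay. Those other measures do not use GAPDH, and the comet procedure itself exposes AP sites.

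A reader might infer more: that because Hypothesis D expects expression of energy-metabolism genes to change, the denominator will move with treatment and this assay is biased between arms. The documents do not support that. The aim under Hypothesis D is confined to muscle and adipose tissue, nothing shows that GAPDH responds to the intervention, and the sizes in the table are assumed. Bias is a possibility under the literal reading and has not been demonstrated. A reader might also take 300 ng as a fixed load that makes normalisation unnecessary, but it is given only as the least amount needed.

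**Conclusion.** The point holds in a limited form. The stated normaliser does not match the assay: a measure of AP sites per base of DNA needs a DNA denominator, and expression is not one. That conclusion rests on the text alone.

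Taken literally, the rule adds the variation of GAPDH expression to the result. It adds bias only on the further condition that the intervention changes GAPDH expression in the assayed cells, which the documents neither show nor exclude. On an assumed 10% change in expression the distortion is about -9% or +11%, and a true 10% fall in AP sites would vanish if expression also fell by 10%.

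The consequence is minor. It touches one of several DNA-damage assays in a secondary, descriptive outcome and leaves the primary endpoint and the sample size untouched. It is still worth correcting, because DNA oxidative damage is part of Aim A2 and validating its measurement is a stated purpose of this pilot.

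**What to change.** Replace the normalisation sentence in the paragraph on baseless sites with:

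> AP-site signal is normalised to the measured mass of DNA loaded in each slot (or to a DNA-based loading control such as a genomic GAPDH probe) and reported as AP sites per number of bases.

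If a genomic GAPDH probe was intended all along, name it as such and drop the word *expression*. Do not write in a fixed load of 300 ng, since the protocol states that figure only as a minimum.

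The cost is one methods sentence, plus measuring and recording the DNA amount for each slot where that is not already done, or running the DNA-based control. No change to the design, the sample size or the main analysis is needed.
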